**Fig. 2 Fig2:**
[figure not shown]
Schedule of enrolment, interventions, and assessments

## Statistical Procedures

### Analysis of Outcome Variables

The primary outcome measure of the study is the proportion of treatment responders at post-treatment rated by the CGI-I. We dichotomize the variable so that treatment responders are defined by a rating of 1 or 2 (markedly or moderately improved from baseline) and non-responders by a rating of 3 or higher [5, 22]. The secondary outcome variables are changes in the mean scores of LSAS and SPIN from baseline to post-treatment. In addition, the primary and secondary outcome variables will be analyzed at 6-month follow-up to examine changes from baseline to follow-up assessment.

### Statistical Analyses

Data will be analyzed with the SPSS statistical software package. All statistical analyses will be conducted on the intent-to-treat (ITT) sample and completer sample. Patients allocated to treatments will be classified as drop-outs if they miss more than 25% of the sessions. In the ITT analyses of treatment response, drop-outs will be considered as failures. In ITT analyses of dimensional measures, missing data will be replaced using the last observation carried forward approach for missing intervention- and post-assessments or follow-up observations. Analyses of the primary outcome measure (CGI-I), a categorical variable, will be conducted using χ^2^ or Fisher's exact tests. Dimensional measures will be submitted to analyses of covariance (ANCOVAs) in which pre-treatment scores will be controlled for. ANCOVAS will be performed separately for the post-treatment and 6-month follow-up assessments. Significance levels will be set at *p* < 0.05, two-tailed. Predictor analysis will be calculated by using logistic regression analysis with CGI-I as the dependent variable; independent variables are competencies, adherence, allegiance, and therapist-rated therapeutic relationships (therapist predictors), as well as patients’ preferred learning style at pre-treatment, changes in insight in SAD-related beliefs and cognitions, and patient-rated therapeutic relationships (patient predictors). Differences between treatments in the outcome predictions will be analyzed, with treatment interactions for each predictor. To test for possible therapist differences, a preliminary analysis of covariance will be conducted. As recommended, significance level in this case will be set at *p* < .30 [37]. If the effect is significant, a multilevel analysis using a mixed-model design is planned to include therapists as a random term [38]. A final analysis will be run to compare the pattern of results from both strategies of analysis taking possible therapist effects into consideration.

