### Selection of Patients

Patients will be included if they meet the following criteria:
primary diagnosis of SAD (German SKID modified for DSM-5)age 18–70 yearsno concurrent psychopharmacological or psychotherapeutic treatmentwritten informed consent must be available before study participation

Patients presenting with any of the following criteria will not be included in the study:
acute suicidalityactive substance abuse or dependence within the past 3 monthssevere depressionpsychotic disorderbipolar disorderborderline personality disorderorganic mental disorder and/or severe medical conditions

Patients may be withdrawn from the study for the following reasons:
on request of the patient (withdrawal of the patient’s consent)if continuation of the study would be detrimental to the subject’s well-beingoccurrence of exclusion criteria

The investigator will decide whether to withdraw patients from the study in cases of 2) and 3). There are no specific plans to promote participant retention. Participants who discontinue will be asked to complete all assessments.

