Standard CT comprises similar elements in the first and third stage of therapy; however, in the middle stage (stage 2), discussion techniques of challenging dysfunctional beliefs are used instead of BE. The techniques are described in detail in the previous manual [17] and include Socratic dialogue, the downward arrow technique, the prejudice technique, the life chart technique, positive data log, automatic thoughts protocol, and the pie chart technique. Dysfunctional beliefs associated with early experiences are identified and discussed. Homework mainly focuses on automatic thoughts and the practice of Socratic dialogue.

In standard CT, therapists are not encouraged to use BEs. Neither exposure based on a habituation rational nor formal social skills training is used.

To equalize therapists’ contact time and treatment dose, both treatments comprise the same amount of contact hours. In line with short-time-therapy in Germany, 25 units of 50-min duration are provided. In CT + BEs, up to eight sessions last 100 min due to the implementation of BEs. Standard CT includes one session of 100-min duration. Thus, the total number of sessions differs (17 vs. 25). The length of both treatments, however, is 6 months, since booster sessions are conducted (4-week interval) in the end of CT + BEs as prescribed in the manual.

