In addition, symptoms of depression will be assessed by independent ratings conducted according to the German version of the Quick Inventory of Depressive Symptomatology (QIDS; 16-item version) [28] and the Beck Depression Inventory (BDI-II) [29]. For both inventories we will use total score to examine changes from baseline to post-treatment and to follow-up assessment.

Each outcome measure will be completed at the pre-treatment, at post-treatment and 6-month follow-up.

Clinical ratings are administered by independent raters blinded to condition. Raters will be trained to perform CGI, LSAS, QIDS, and BABS assessments. The interviews will be videotaped to review and assess inter-rater reliability between independent raters.

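### The ITT response analysis scores low attenders as failures even when a blinded CGI-I rating exists, using a session cut-off that is not equivalent in contact time between the arms

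*Protocol article*

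**What the plan says.** All references are to the protocol article.

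- **Primary outcome (Analysis of Outcome Variables).** "The primary outcome measure of the study is the proportion of treatment responders at post-treatment rated by the CGI-I". Response is a rating of 1 or 2; attendance is not part of the definition. Response is also analysed at 6-month follow-up.
- **Drop-out (Statistical Analyses).** "Patients allocated to treatments will be classified as drop-outs if they miss more than 25% of the sessions".
- **Scoring (Statistical Analyses).** "In the ITT analyses of treatment response, drop-outs will be considered as failures". For dimensional measures, by contrast, last observation carried forward is applied only to missing data.
- **Analysis sets (Statistical Analyses).** "All statistical analyses will be conducted on the intent-to-treat (ITT) sample and completer sample".
- **Assessment after stopping (Selection of Patients).** "Participants who discontinue will be asked to complete all assessments".
- **Raters (Outcome Measures).** "Clinical ratings are administered by independent raters blinded to condition".
- **Schedule (Treatments).** Both arms are meant to receive 25 units of 50 minutes over 6 months. CT plus BEs has up to eight 100-minute sessions and standard CT has one, giving 17 and 25 sessions. CT plus BEs reaches 6 months "since booster sessions are conducted (4-week interval) in the end of" that treatment.

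**The concern.** The rule ties failure to attendance rather than to a missing outcome. The trial would collect a blinded rating from a patient who stopped early and then replace it with non-response. The completer sample does not restore that patient's rating, so neither planned analysis uses it. The same patient's observed LSAS and SPIN would still enter the ITT analysis of those measures, so one patient could contribute real data to the secondary outcomes and an imposed value to the primary one. The rule also reaches follow-up response: a patient rated very much improved at 6 months would still count as a failure.

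The cut-off is also counted in sessions, although the arms deliver the same intended dose in different numbers of sessions of different length. Equal non-attendance, measured in therapy time or in calendar time, can therefore be classified differently by arm. With 30 patients per arm, a few reclassified patients matter.

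**Working it through.** **Inputs from the protocol article:** cut-off of more than 25% of sessions; 17 and 25 sessions; 25 units of 50 minutes; up to 8 double sessions in CT plus BEs and 1 in standard CT; 30 patients per arm; expected drop-out of 10% (Design and Sample Size). The article states no figure for the effect of this rule, so there is none to reproduce.

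**Step 1. Cut-off in sessions.**
- CT plus BEs: 0.25 × 17 = 4.25, so failure starts at 5 missed sessions (5/17 = 29.4%).
- Standard CT: 0.25 × 25 = 6.25, so failure starts at 7 missed sessions (7/25 = 28.0%).

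**Step 2. Cut-off in contact time.**
- CT plus BEs with all eight double sessions: 9 + 8 × 2 = 25 units. Missing five single sessions is 5/25 = 20% and counts as failure. Missing four double sessions is 8/25 = 32% and does not. Five missed sessions can be anything from 5 to 10 units, 20% to 40% of the dose.
- Standard CT: 25 sessions with one double make 26 units, whereas 25 units would be 24 sessions. The Treatments section does not reconcile the two, but 0.25 × 24 = 6 also gives a cut-off of 7. Seven missed sessions are 7 or 8 units: 27% to 31% of 26, or 28% to 32% of 25.

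**Step 3. Effect on the comparison.** Let d1 and d0 be the shares of patients over the cut-off in CT plus BEs and standard CT, and q1 and q0 the response rates they would have on observed ratings. The shift in the response difference (CT plus BEs minus standard CT, scored minus observed) is d0·q0 − d1·q1. It is zero if both quantities are equal across arms. The article gives neither, so the following are illustrations on stated assumptions.

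*Stopping at a calendar time.* Assume CT plus BEs has 14 weekly sessions and then 3 at four-week intervals, standard CT has 25 weekly sessions, and stopping is uniform over 26 weeks.
- A stop after any of weeks 13 to 18 leaves 4 to 2 of 17 sessions missed in CT plus BEs (24% to 12%, kept) and 12 to 7 of 25 in standard CT (48% to 28%, failure). Earlier stops are failures in both arms; later stops are kept in both.
- Share of stoppers over the cut-off: 12/26 in CT plus BEs and 18/26 in standard CT.
- With 10% stopping and 60% response among stoppers, all of them rated: 0.60 × 0.10 × (18/26 − 12/26) = 0.0138, about +1.4 points, favouring CT plus BEs. That is about 0.4 of a patient in an arm of 30.

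*Scattered absences.* Assume the same independent chance of missing each session in both arms, and again 60% response among those over the cut-off.

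| Chance of missing a session | CT plus BEs, P(5 or more of 17) | Standard CT, P(7 or more of 25) | Shift, 0.60 × (standard CT − CT plus BEs) |
|---|---|---|---|
| 10% | 2.2% | 0.9% | −0.8 points |
| 15% | 9.9% | 7.0% | −1.8 points |
| 20% | 24.2% | 22.0% | −1.3 points |
| 25% | 42.6% | 43.9% | +0.8 points |

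For most of this range the shift is against CT plus BEs; at 25% the sign changes.

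**Step 4. Weight of one patient.** 1/30 = 3.3 points. For illustration, 20/30 against 13/30 responders gives p = 0.069 by uncorrected χ²; rescoring one standard-CT responder (20 against 12) gives p = 0.038. By Fisher's exact test, which the article also allows, the same change moves p from 0.119 to 0.069.

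**The case against.** Counting non-completion as failure is a familiar conservative convention, and a composite of response and adequate attendance is a legitimate outcome if declared. Here it is not declared: the outcome is defined by the CGI-I alone and the analysis is called ITT.

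A reader might infer that the rule does bias the primary comparison, or that it favours CT plus BEs because patients who improve early and stop are failures in one arm and responders in the other. The documents do not support that. The cut-offs are almost the same as shares of sessions. The calendar contrast rests on an assumed schedule: the text gives neither the number of boosters nor which sessions are weekly, the schedule figure is not available here, and eight double sessions is a maximum. Even on that schedule the contrast covers only stops in weeks 13 to 18. Scattered absences mostly push the other way.

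The effect is also limited at the article's own 10% drop-out figure. No special retention measures are planned, so some stoppers will have no rating, and for them the rule overwrites nothing. The dimensional analyses keep observed scores.

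These points remove the claim of a known bias. They leave standing that the rule discards observed primary-outcome ratings and that its cut-off does not mean the same amount of therapy in the two arms.

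**Conclusion.** The point holds in a limited form and should be fixed, though it does not by itself invalidate the design. Two parts follow directly from the text: an available blinded CGI-I, at post-treatment or follow-up, is replaced by failure on attendance alone, which is not ITT on the stated outcome and is inconsistent with the handling of the dimensional measures; and the session-based cut-off is not equivalent in contact time.

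The consequence for the treatment comparison is a possible bias of unknown direction. The 1.4-point figure is illustrative and depends on the assumed calendar, uniform stopping, 60% response among stoppers and a rating for every stopper. No bias arises if the share over the cut-off and the response among those patients are equal in the two arms.

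**What to change.** 1. In the ITT response analyses at post-treatment and follow-up, use the observed CGI-I for every randomised patient who has one, whatever their attendance. Count as failure only patients whose rating is missing. Multiple imputation is optional as a sensitivity analysis; with 60 patients it is not essential.
2. If the attendance-based failure rule is wanted, keep it as a named sensitivity analysis.
3. Define the completer sample by the share of 50-minute contact units, with the same threshold in both arms. More than 25% of 25 units means 7 or more units missed. First reconcile the standard CT figures (25 sessions including one double make 26 units).

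The cost is a change of wording and one extra analysis. No new data are needed, because assessments after discontinuation are already requested and therapists already record contact time after each session. The drawback is that the primary response rates no longer represent a worst case for low attenders; that role passes to the sensitivity analysis. The change should be made before any unblinded analysis.

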The SCQ (Social Cognition Questionnaire) [35] (German translation [36]) is a self-report measure to assess the frequency and intensity of SAD-related cognitions. The questionnaire will be completed by the patients at every session.

Detailed procedure of the measurements is listed in the schedule of enrolment, interventions and assessments (Fig. 2).

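### In the ITT analyses of LSAS, SPIN, BABS, QIDS and BDI-II, last observation carried forward turns a missing post-treatment score into zero change and can bias the arm difference in either direction

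*Protocol article*

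**What the plan says.** Statistical Analyses first sets the populations: "All statistical analyses will be conducted on the intent-to-treat (ITT) sample and completer sample". For dimensional measures in the ITT sample the rule is that "missing data will be replaced using the last observation carried forward approach for missing intervention- and post-assessments or follow-up observations". The model is also fixed: "Dimensional measures will be submitted to analyses of covariance (ANCOVAs) in which pre-treatment scores will be controlled for", and "ANCOVAS will be performed separately for the post-treatment and 6-month follow-up assessments". The section names no other method for missing dimensional data.

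Outcome Measures gives the schedule: "Each outcome measure will be completed at the pre-treatment, at post-treatment and 6-month follow-up". Analysis of Outcome Variables names the outcomes most exposed: "The secondary outcome variables are changes in the mean scores of LSAS and SPIN from baseline to post-treatment", with the follow-up analysed as well.

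Two measures are handled differently. For CGI-I response, "In the ITT analyses of treatment response, drop-outs will be considered as failures". For the SCQ, Additional Assessments says that "The questionnaire will be completed by the patients at every session".

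On retention, Selection of Patients says that discontinuers will be asked for all assessments and that no specific retention measures are planned. Design and Sample Size expects 10% drop-out.

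**The concern.** With three assessments, the only LSAS or SPIN value before post-treatment is the baseline. Carrying the last observation forward therefore has these effects:

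- **Post-treatment missing:** the pre-treatment score is entered as the outcome. The same number is also the ANCOVA covariate for that patient.
- **Only follow-up missing:** the post-treatment score is entered, so neither relapse nor further gain is allowed for.
- **Both missing:** the baseline stands in at both visits.

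In each case the filled-in value is analysed as if it had been observed.

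Zero change is an implausible default here because both arms receive active cognitive therapy. Background reports standardised differences against no treatment of 0.97 and 1.56. Those are not changes from baseline, but they show that large improvement is expected. Hypothesis 3, on greater change in symptoms, insight and avoidance, rests partly on these measures. Equal missingness cannot be taken for granted either, since the arms differ in number of sessions (17 against 25) and in session length (Treatments).

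**Working it through.** The plan gives no figure for the effect of this rule, so there is none to reproduce. The calculation below is an illustration.

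**Inputs from the protocol article:** planned difference 0.60 SD, used only as a yardstick; 30 patients per arm; expected drop-out 10% (all from Design and Sample Size).

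**Assumptions not in the document:** mean improvement c = 1.0 to 1.4 SD in standard CT and c + 0.60 in CT plus BEs; missing patients would have improved like the others; the split of missing scores between arms.

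**Formula.** A patient with a missing post-treatment score contributes zero change, so an arm with missing proportion m shows (1 - m) times its true improvement. The bias of the difference (CT plus BEs minus standard CT) is

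bias = m_CT × c - m_BE × (c + 0.60).

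| Missing CT+BEs / standard CT | c = 1.0 | c = 1.4 | Estimate in place of 0.60 |
|---|---|---|---|
| 10% / 10% | 0.10 - 0.16 = -0.06 | 0.14 - 0.20 = -0.06 | 0.54 |
| 15% / 5% | 0.05 - 0.24 = -0.19 | 0.07 - 0.30 = -0.23 | 0.41 to 0.37 |
| 5% / 15% | 0.15 - 0.08 = +0.07 | 0.21 - 0.10 = +0.11 | 0.67 to 0.71 |
| 20% / 10% | 0.10 - 0.32 = -0.22 | 0.14 - 0.40 = -0.26 | 0.38 to 0.34 |
| 10% / 20% | 0.20 - 0.16 = +0.04 | 0.28 - 0.20 = +0.08 | 0.64 to 0.68 |

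The first three rows average the planned 10%; the last two average 15%. In patients, 10% of 30 is three per arm.

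**No true difference.** If both arms improve by c, a 10-point imbalance gives 0.10 × c = 0.10 to 0.14 SD, against the arm with more missing scores.

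**If missing patients would have improved less.** Take 10% missing in both arms and half the improvement in missing patients. The true difference over all randomised patients is then 0.60 × (0.90 + 0.05) = 0.57, and carrying forward gives 0.54, a shrinkage of about 5%. If they would not have improved at all, the true difference is 0.60 × 0.90 = 0.54 and the mean is unbiased.

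**Check with the planned ANCOVA.** A simulation used 6,000 runs, 30 per arm, an assumed pre-post correlation of 0.5 and scores missing completely at random. Improvements of 1.56 and 0.97 SD (true difference 0.59) stood in for change from baseline.

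- 10% missing in both arms: carrying forward gave 0.53 with power of about 58%. ANCOVA on observed scores gave 0.59 with about 68%.
- 15% in CT plus BEs and 5% in standard CT: 0.41. Reversed: 0.65.
- No true difference (1.265 SD in both arms), 15% and 5% missing in either direction: about 0.13 SD and a type I error of about 8%. With 20% and 0%: 0.25 SD and about 18%.
- ANCOVA on observed scores stayed near zero bias and 5% in these null settings.

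**The case against.** The strongest reply is that the exposure is limited, and much of that stands. These are secondary and additional outcomes. Drop-out is defined by missing more than 25% of sessions, not by a missing score, and discontinuers will be asked to complete assessments, so missing scores may be fewer than the 10% drop-out. A completer analysis runs alongside, and a mixed model is foreseen.

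These provisions do not repair the ITT estimate. The completer sample is selected on attendance after randomisation. The mixed model is conditional on a therapist check at p < .30 and addresses therapist effects only. Asking for assessments, without retention measures, does not secure them.

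A reader might infer more than the documents support:

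- **That the primary outcome is biased by this rule.** CGI-I response counts drop-outs as failures. The Abstract does call LSAS the primary outcome, but Outcome Measures and Analysis of Outcome Variables both name CGI-I; that mismatch is a separate matter.
- **That every dimensional measure falls back to baseline.** The SCQ, taken each session, would carry a later value.
- **That the bias is the difference in missing proportions times mean improvement, even with a true effect of 0.60.** That product holds only when both arms improve equally. With a true difference the bias is asymmetric, as the table shows.
- **That standard errors are shown to be too small.** Treating filled-in values as observed is wrong in principle. With equal missingness and no true difference, however, the simulated rejection rate was 5.5%, the same as with complete data. The error inflation found came from unequal missingness.

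**Conclusion.** The concern holds for the ITT analyses of LSAS, SPIN, BABS, QIDS and BDI-II. The rule and the schedule together impose zero change on anyone without a post-treatment score. At 10% missing in both arms the loss is modest: 0.60 falls to 0.54, or less is lost if missing patients would have improved less. The larger risk is imbalance. A 10-point difference moves a true 0.60 by about -0.19 to -0.26 SD when CT plus BEs has more missing scores, and by about +0.04 to +0.11 SD when standard CT has more. It creates 0.10 to 0.14 SD where there is no true difference. Since the direction is not fixed, the rule cannot be defended as conservative.

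These sizes rest on the assumed improvements and missing proportions; the mechanism needs only some missing post-treatment scores and real improvement. It would go too far to say that the tests of Hypothesis 3 merely reflect who returned for assessment, because about 90% or more of scores are expected to be observed. This should be corrected, but it does not threaten the primary analysis.

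**What to change.** In Statistical Analyses, replace last observation carried forward as the main ITT method for dimensional measures with one of the following:

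1. Multiple imputation using baseline, arm and the observed post-treatment and follow-up scores, followed by the planned ANCOVAs at each time point.
2. A likelihood-based repeated-measures model with baseline, post-treatment and follow-up all in the outcome vector. Baseline must be an outcome here: with baseline only as a covariate, a patient missing both later visits contributes no row, and the analysis no longer covers all randomised patients.

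Keep carrying forward at most as a sensitivity analysis. The CGI-I rule needs no change for this point.

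The cost is a change of wording and slightly more analysis work, with no new data; the section already foresees a mixed model. The price is reliance on a missing-at-random assumption, which should be stated. Whether therapist belongs in the model unconditionally, and what to do about data missing not at random, are separate questions and not part of this change.

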**Fig. 1 Fig1:**
[figure not shown]
Study flowchart. Flowchart of planned participants’ selection and study design

The study is designed to detect a moderate effect size (d = 0.60, f = 0.35), as observed in the meta-analysis for CT for SAD with intense BE and prolonged sessions, as compared to CT with a reduced number of BEs and shortened sessions [7]. A power analysis with 90% power on a two-sided test where α = 0.05 revealed a sample size of *N* = 54 (27 per group). Based on data from previous studies [5], we expect a drop-out rate of 10%. Thus, 60 patients (30 per group) will have to be recruited.

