### Outcome Measures

The primary outcome measure is treatment response between baseline and posttreatment as assessed by the improvement item of the Clinical Global Impression Scale (CGI) modified for individuals with social anxiety disorder [21]. The CGI is a standard primary outcome measure in psychopharmacologic studies and has two components. The CGI-Severity (CGI-S) contains a Severity of Illness item that provides information about the current severity of social phobic symptoms. The severity rating is made by a clinician on a seven-step categorical scale with 1 representing “normal” or “not at all ill” and 7 representing “among the most severely ill patients”. The CGI-Improvement (CGI-I) rates the change in symptom severity and impairment from the baseline, ranging from 1 (“very much improved”) to 7 (“very much worse”). The psychometric properties of CGI have been found to be very good [5, 22]. The clinical raters assigned to each treatment condition will complete CGI-S at pre-treatment and CGI-I at post-treatment and 6-month follow-up assessment. Patients rated 1 or 2 (markedly or moderately improved from baseline) will be classified as responders, and those rated 3 or higher will be classified as non-responders.

The secondary outcome measures will be changes in the clinician-rated Liebowitz Social Anxiety Scale (LSAS) [23] and the patient-rated Social Phobia Inventory (SPIN) [24] from baseline to post-treatment. The LSAS assesses fear in and avoidance of 24 social situations in the last week, rated on 4-point scales ranging from 0 (non and never) to 4 (severe and usually) of. In the current study we will use the total score by summing both subscales. The SPIN consists of 17 items evaluating fear, avoidance, and physiological discomfort in the last week on a 5-point rating scale, ranging from 0 (not at all) to 4 (extremely). The total score is obtained by adding up the answers of the individual items.

Changes in insight in SAD-related beliefs from baseline to post-treatment and follow-up assessment will be assessed using the German version of the clinician-administered Brown Assessment of Beliefs Scale (BABS) [25–27]. The scale consists of seven items rating the degree of conviction and insight of beliefs from 0 to 4. The outcome measure will be the total score of the first six items.

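### The primary CGI-I responder test leaves collected baseline severity unused and does not choose between chi-square and Fisher: a modest loss of efficiency, not bias

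*Protocol article*

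**What the plan says.** Under Analysis of Outcome Variables, the article defines the endpoint: "The primary outcome measure of the study is the proportion of treatment responders at post-treatment rated by the CGI-I". Ratings of 1 or 2 count as response. (The abstract names the LSAS as primary instead. This point takes the definition in the body of the article.)

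Under Statistical Analyses, "Analyses of the primary outcome measure (CGI-I), a categorical variable, will be conducted using" chi-square or Fisher's exact tests. No covariate and no selection rule is given. The next sentence treats the other outcomes differently: "Dimensional measures will be submitted to analyses of covariance (ANCOVAs) in which pre-treatment scores will be controlled for". The logistic regression described further on is a predictor analysis and does not list baseline severity among its predictors.

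Baseline severity is available. Under Outcome Measures, the raters "will complete CGI-S at pre-treatment and CGI-I at post-treatment and 6-month follow-up assessment", and "Each outcome measure will be completed at the pre-treatment, at post-treatment and 6-month follow-up". Study Procedures also places the LSAS at the screening visit, before randomisation.

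The same section describes the primary scale as a change rating: "The CGI-Improvement (CGI-I) rates the change in symptom severity and impairment from the baseline".

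**The concern.** Hypothesis 1 is the trial's main hypothesis, yet it is the one outcome analysed without the baseline information that the plan uses elsewhere. With 30 patients per arm, and no stratification by severity described under Randomization, the arms may differ in severity by chance. If severity predicts response, part of that difference carries into the primary comparison and some precision is lost.

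The plan also names two tests. They share a nominal 5% level but do not behave alike at this sample size. Without a rule, the choice could be made after the table is seen, and for some tables it decides whether the result is called significant.

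**Working it through.** **Inputs from the article.** 30 per arm; drop-outs count as failures in the ITT response analysis, so all 30 are analysed. Two-sided alpha is 0.05. The design effect is d = 0.60.

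**Assumptions.** The article gives no response rates and no correlation between baseline severity and response. I take control response rates of 30% to 70%, carry d = 0.60 over as a probit shift, p1 = Φ(Φ⁻¹(p0) + 0.60), and vary the correlation r from 0 to 0.5.

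**1. The plan's own figure.** The article states "A power analysis with 90% power on a two-sided test" at alpha 0.05, giving N = 54. For a two-sided comparison of means, n per arm = 2(1.960 + 1.282)²/d².
- d = 0.60: 2 × 10.51/0.36 = 58.4, so 59 per arm (118 in total).
- f = 0.35 means d = 2f = 0.70: 2 × 10.51/0.49 = 42.9, so 43 per arm (86 in total).

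Neither gives 54; only the inflation 54/(1 − 0.10) = 60 reproduces. The formula is also for means, not for a responder test. That is a separate point; here it means the article offers no power figure for the test it plans.

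**2. Chi-square against Fisher, by exact enumeration.** Rejection probability = Σᵢ Σⱼ Bin(i; 30, p0) × Bin(j; 30, p1) × 1[test rejects table (i, j)].

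| Control vs experimental | Uncorrected chi-square | Fisher |
|---|---|---|
| 50% vs 50% (size) | 5.2% | 2.7% |
| 30% vs 53.0% | 44.3% | 34.2% |
| 40% vs 63.6% | 45.9% | 35.6% |
| 50% vs 72.6% | 43.3% | 33.4% |
| 65% vs 83.8% | 38.6% | 28.6% |
| 70% vs 87.0% | 35.7% | 25.2% |

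For null rates of 30% to 80%, size is 4.8% to 5.2% for chi-square and 2.2% to 2.7% for Fisher. The largest chi-square size at any rate is 5.5%. The power gap is about 10 points throughout. Chi-square with continuity correction has the same size and power as Fisher here.

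**3. Where the tests disagree.** Every table that Fisher rejects is also rejected by uncorrected chi-square (no exceptions); 54 tables are rejected by chi-square only. Taking the smaller p-value is therefore the same as using chi-square. Example: 15/30 vs 23/30. Pooled rate = 38/60 = 0.633; X² = (8/30)²/(0.633 × 0.367 × 2/30) = 0.0711/0.0155 = 4.59, p = 0.032. Fisher gives p = 0.060.

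**4. Gain from adjustment.** Simulation with 4,000 trials per setting, 30 per arm, control response 50%, latent d = 0.60 and one baseline covariate with correlation r to the latent response. The adjusted test is the penalised (Firth) likelihood-ratio test.

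| r | Penalised logistic | Chi-square, same trials | Gain |
|---|---|---|---|
| 0 | 42.7% | 42.8% | −0.1 |
| 0.3 | 44.7% | 43.6% | 1.1 |
| 0.4 | 47.1% | 43.2% | 3.9 |
| 0.5 | 48.6% | 41.9% | 6.7 |

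The Monte Carlo error of a single power figure is √(0.45 × 0.55/4000) = 0.8 points. Across repeated runs the gain is about 0 to 1.5 points for r up to 0.3 and about 6 points at r = 0.5, with size held near 5%. An unpenalised likelihood-ratio test shows more (47.3% vs 44.4% at r = 0.3; 51.8% vs 44.6% at r = 0.5), but part of that comes from its own size of 5% to 6%.

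**The case against.** An unadjusted comparison of two proportions is valid under randomisation and conventional for a binary endpoint. Nothing in the article contradicts it, and the parallel with ANCOVA is incomplete. ANCOVA gains most when the same scale is measured twice, whereas CGI-I is itself a rating of change and has no pre-treatment value. Its correlation with baseline severity may be low, and then adjustment gains almost nothing. This stands, and it limits the claim to efficiency and chance imbalance. It does not remove the claim, because a change rating can still depend on initial severity.

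Naming both tests is often shorthand for the expected-count rule. With 30 per arm the smallest expected cell is 30 × min(p, 1 − p), which falls below 5 only if the pooled rate is under 5/30 = 16.7% or over 83.3%. At every pair of rates in the table above, that rule would point to chi-square. The rule may stand in a fuller document that is not shown. It is not in the article, however, and one clause would settle it.

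A reader might infer three stronger things that the article does not support. The first is that the primary result is biased; randomisation rules that out. The second is that picking the test afterwards inflates false positives; the nesting in step 3 shows that it cannot exceed chi-square's own size. The third is that adjustment would rescue the trial's power; under these assumptions it stays near 50% even at r = 0.5.

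**Conclusion.** The point holds in a limited form. The primary analysis leaves available baseline severity unused and does not fix which of two tests applies.

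The test choice is the firmer half. At 30 per arm Fisher runs at about half the nominal level and gives up about 10 power points. The gap is nearly constant for control response rates of 30% to 70%, so it depends little on the assumed rates. The consequence is a possibly data-dependent verdict in borderline tables, without inflation of the error rate beyond that of chi-square.

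The adjustment half is conditional: about 0 to 1.5 points of power at r up to 0.3 and about 6 points at r = 0.5. The article gives nothing from which to judge r. Adjustment is worth making because the data are already collected and it deals with chance imbalance, not because a large gain can be promised.

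**What to change.** Under Statistical Analyses, replace the two-test wording for the primary outcome with one prespecified analysis: logistic regression of CGI-I response at post-treatment on treatment and one baseline severity score (LSAS or CGI-S, named before outcome data are seen). Fit it by penalised likelihood and report the standardised risk difference with its 95% CI. Keep the chi-square test as the sensitivity analysis, stated to be without continuity correction, and drop Fisher as an open alternative.

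The change needs wording only: no new patients, visits or measurements. The costs are a slightly more complex model, little gain if baseline severity predicts response weakly, and a check that the named software (SPSS) can fit the penalised model, or the naming of another program. If the planned therapist mixed model is triggered, it should carry the same covariate so that the two analyses remain comparable. The sample size still has to be reconciled separately with the responder endpoint.
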